#### Gender role conflict

The Restrictive Emotionality subscale of the Gender Role Conflict Scale - Adolescent Version (GRCS-A) [33] will be used to assess conformity to gender norms. The sub-scale contains 9 items that are rated on a 6-point scale ranging from 1 (strongly disagree) to 6 (strongly agree). Total scale scores can range from 9 to 54, with higher score indicative of greater conformity to gender norms regarding emotional restriction.

#### Confidence supporting peers

Four items, adapted from literature evaluating the Mental Health First Aid (MHFA) training program [34], will be used to assess respondents’ confidence and willingness to support a friend or peer who is experiencing personal difficulties. Responses are on a 5-point scale from 1 (not at all) to 5 (extremely) or a Yes/No/Don’t know scale.

In addition to the measures above, participants in intervention schools will be asked to complete a number of open-ended evaluation questions at post-intervention. These qualitative data will provide insight into strengths and areas of improvement for the Silence is Deadly program.

### Sample size and power calculations

A sample of 800 adolescents from 8 high schools (100 students per school) will be targeted for recruitment to the current study. Calculation of the required sample size was based on detecting a small-moderate post-intervention effect size of f = 0.2. Assuming correlation between repeated measures of 0.5, intra-class correlation of 0.03 (accounting for clustering within schools) and 20% attrition, the trial will have >85% power to find a small difference (Cohens f = 0.2) between groups.

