### Gender specific attitudes to help-seeking must be addressed

It is increasingly recognised that in order to improve rates of help-seeking among men, public health interventions must address the underlying attitudes and norms held by men that predicate planned behaviour [3, 4]. Young men are known to hold more negative attitudes towards help-seeking for mental health issues than young women [5], due in part to lower levels of openness to acknowledging psychological problems [6]. These differences in psychological openness are thought to be due to subjective masculine norms that encourage emotion suppression and lead to the stigmatisation of help-seeking for emotional problems [7].

This account is strengthened by research finding that up to 59% of the variance in mental health help-seeking attitudes among men can be explained by stigma and gender role conflict [8]. Further, a recent large all-male cohort study found that conformity to masculine norms around self-reliance and help-seeking was a significant predictor of increased risk of suicidal thinking [9]. Thus in order to change help-seeking behaviours, these norms and attitudes must be addressed. A recent systematic review of help-seeking interventions for depression, anxiety and psychological distress found promising evidence for the effectiveness of mental health literacy interventions in changing attitudes towards help-seeking (*d* = .12 to .53), particularly in young people [10]. However, none of the studies identified in this review analysed results according to gender and none were tailored to address the gender-based attitudes and perceived norms thought to drive male help-seeking behaviour.

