### Recruitment

At least 8 ACT schools, totalling approximately 800 students (100 male students per school), will be recruited to the trial via pre-existing relationships with the intervention provider Menslink. Due to Menslink’s longstanding involvement in the ACT community, providing services to school-aged males, the organisation has existing relationships with almost all schools in the region that enrol male students.

The research trial will be advertised via invitational letters and direct contact from Menslink staff to ACT schools with male students in grades 11 and 12 (16–18 years). Information and consent forms will be distributed to all participants prior to the completion of the pre-intervention survey, with participants aged 16 years and older being able to provide informed consent as a ‘mature minor’ [20]. If an insufficient number of participants can be drawn from this age group (16–18 years) then the sample will be extended to include males in Years 7 to 10 (12–16 years), and parental consent will be collected in addition to participant assent. All male students in participating schools could potentially attend the Silence is Deadly program, but only consenting students will be invited to complete the trial surveys.

Up to three staff members per school will be invited to participate in a semi-structured interview. The staff members targeted for this aspect of the research will be those holding key leadership and student wellbeing positions, such as year group coordinators, school psychologists and deputy principals.

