### Randomisation

Each school will be cluster-randomised into either the intervention or wait-list control condition. This approach will reduce school and administrative burden and prevent contamination of the wait-list control condition. Randomisation will be conducted by a statistician who is not involved in the day-to-day management of the trial according to ICH Guidelines [21]. Given that entire schools will be randomised, a minimisation approach to randomisation will be taken in order to balance participant characteristics and numbers across conditions [22, 23]. Two factors will be used in the minimisation process: school type (private vs. public) and the number of students in grades 11 and 12 (<300 vs. 300+).

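### The >85% power stated for 8 schools rests on large-sample degrees of freedom or on unstated stability of school effects; on about 6 df it is roughly 64–80% for d = 0.4

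*Protocol article*

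**What the plan says.** All the inputs stand in the section Sample size and power calculations:

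- Target: "A sample of 800 adolescents from 8 high schools (100 students per school) will be targeted for recruitment".
- Effect: the calculation was "based on detecting a small-moderate post-intervention effect size of f = 0.2".
- Other inputs: "Assuming correlation between repeated measures of 0.5", with "intra-class correlation of 0.03 (accounting for clustering within schools) and 20% attrition".
- Result: "the trial will have >85% power to find a small difference (Cohens f = 0.2) between groups".

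The section Randomisation makes the school the randomised unit, in two arms, by minimisation. The section Statistical analysis specifies a mixed-model repeated-measures analysis with random effects for school. The section Recruitment gives the number of schools as a minimum: "At least 8 ACT schools, totalling approximately 800 students (100 male students per school").

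The power section gives no alpha, formula or degrees of freedom. It also does not say whether the correlation of 0.5 applies to students only or to school means as well.

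**The concern.** Inflating the variance by a design effect allows for students in one school resembling each other. It does not allow for the school-level variance being estimated from only 8 schools. With so few clusters the reference distribution matters: the two-sided 5% critical value is 2.45 on 6 df, against 1.96 for the normal. If the quoted power was read off a large-sample distribution, it is too high for a test that holds its 5% level. Conversely, using 1.96 on 6 df would give a true type I error near 9.8%.

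The label adds to the problem. Consecutive sentences call the same f = 0.2 small-moderate and then small, and for two equal groups it is d = 0.4. A reader told that the trial has high power for a small difference could take a null result as stronger evidence against small effects than the design allows.

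**Working it through.** **Inputs from the article:** 8 schools; 100 students each, 80 after 20% attrition (640 in total); ICC 0.03; repeated-measures correlation r = 0.5; f = 0.2. **Assumed, because not stated:** two-sided alpha 0.05 and 4 schools per arm.

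**Step 1, effect size.** For two equal groups d = 2f = 2 × 0.2 = 0.4.

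**Step 2, effective sample.** Design effect = 1 + (80 − 1) × 0.03 = 3.37. Effective N = 640 / 3.37 = 189.9.

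**Step 3, noncentrality.** ncp = d / √(4v / 189.9), where v is the variance factor:

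- post-only: v = 1; change score: v = 2(1 − 0.5) = 1, so r = 0.5 brings no gain;
- baseline-adjusted: v = 1 − 0.5² = 0.75;
- between-group test averaged over three occasions: v = (1 + 2 × 0.5)/3 = 0.667.

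**Step 4, power at d = 0.4.**

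| Comparison | ncp | Power, about 188 df | Power, 6 df |
|---|---|---|---|
| Post-only or change score | 2.76 | 78% | 64% |
| Baseline-adjusted | 3.18 | 89% | 76% |
| Three-occasion between-group | 3.38 | 92% | 80% |

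The article's figure is therefore reproduced in the 188-df column, in the two rows that credit r = 0.5. The 6 df are 8 schools minus 2 arms. If the design effect is computed on 100 per school (1 + 99 × 0.03 = 3.97) before the 20% loss, effective N is 161. The three powers are then 71%, 83% and 87% with large df, and 57%, 69% and 74% on 6 df.

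**Step 5, stability of school effects.** Step 4 lets school effects correlate 0.5 between waves, like the overall r. Write c for that correlation and keep the overall r at 0.5. The student-level correlation is then (0.5 − 0.03c)/0.97. The variance of a school mean is 0.03 + 0.97/80 = 0.0421, and the covariance of school means between waves is 0.03c + (0.5 − 0.03c)/80. Power at d = 0.4 on 6 df:

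| c | Change score | Baseline-adjusted |
|---|---|---|
| 0.5 | 64% | 76% |
| 0.7 | 77% | 85% |
| 0.8 | 85% | 90% |
| 0.9 | 93% | 95% |
| 1.0 | 99% | 99% |

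**Step 6, detectable difference and smaller effects.** On 6 df, 85% power needs ncp = 3.61. With c = 0.5 the detectable d is 3.61 × √(4v / 189.9): 0.52, 0.45 and 0.43 for the three comparisons. At d = 0.2 the powers are 21%, 27% and 30%.

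**The case against.** A reader might infer that the article made an arithmetic error and that its own inputs give 64–80%. The documents do not support that. The listed inputs do give more than 85% by the usual design-effect formula. The lower range needs two things the article leaves unstated: a test on about 6 df, and school effects correlating only 0.5 between waves. The first follows closely from randomising 8 schools in two arms. The second is open. A single random intercept per school, which is one natural reading of the analysis section, is the case c = 1.0, with power near 99%. So it is not established that the trial falls short of 85%. What stands is that the stated figure depends on a choice the reader cannot see.

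Other routes also pass 85% on 6 df, but for a different quantity from the one stated:

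- Averaging both follow-ups with baseline adjustment (v = 0.5) gives about 90%. This needs d = 0.4 to persist at 3 months, whereas the article names a post-intervention effect.
- A within-between interaction convention gives over 99%. There ncp² = 0.2² × 189.9 × 2/0.5 = 30.4, so ncp = 5.51. In the change-score formula that is a difference in change of 5.51 × 2/√189.9 = 0.8 SD, twice the between-group effect.

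The schools are a minimum of 8. Ten schools of 80 completers would give 77%, 87% and 91% on the Step 4 basis. This is a fair point about the trial, but the power claim is made for 8.

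The method for degrees of freedom is commonly left to an analysis plan. That is accepted, and its absence is not the point here. The point is a published number that depends on it.

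Two further inferences are tempting and should not be drawn:

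- The minimisation factor, "the number of students in grades 11 and 12 (<300 vs. 300" or more), does not show that the analysed clusters will be very unequal. It counts students in two grades, not male participants, and no cluster-size variation is given.
- The review result "in changing attitudes towards help-seeking (*d* = .12 to .53") concerns attitudes, not the primary outcome of intentions, so it is not a benchmark for this effect size.

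**Conclusion.** The point holds in a limited form. For f = 0.2 (d = 0.4) with 8 schools, more than 85% power is obtained from a large-sample calculation that credits r = 0.5. On about 6 df the figure is about 64% (post-only or change score), 76% (baseline-adjusted) or 80% (three-occasion between-group test) if school effects correlate 0.5 over time. The 80% is the generous end, since that test averages in the pre-intervention wave. For the post-intervention comparison, 85% on 6 df requires a school-level correlation of about 0.7 (baseline-adjusted) or 0.8 (change score) or more, which the article does not state.

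These figures assume two-sided alpha 0.05, a 4:4 split and 80 completers in every school. Separately, and whatever the degrees of freedom, f = 0.2 carries two labels. Calling it small overstates what the design can detect.

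**What to change.** Revise the power statement in Sample size and power calculations:

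- Give alpha, the comparison and the test, with a t or F reference on about 6 df for 8 schools, and state the assumed correlation of school effects over time.
- Report power for d = 0.4 as about 64–80% if that correlation is 0.5. Show higher values only beside an explicit stability assumption. Alternatively, report the detectable difference at 85% power on the same basis, d about 0.43–0.52.
- Use one label for the effect and give it as d = 0.4, not as small. Add that power for d = 0.2 is about 21–30% on the same basis.

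The change is to text only and needs no extra schools or students. Its cost is a less favourable stated power, unless the sponsor can justify stable school effects.

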### Statistical analysis

Analyses of primary and secondary effectiveness outcomes will be conducted using a mixed-model repeated measures (MMRM) approach [35], the standard and most robust methodology for analysing randomised controlled trials. This approach is able to include participants with missing data without using biased imputation techniques, assuming that data are missing-at-random. Further, by incorporating appropriate random effects for each school, MMRM can accommodate and assess the strength and significance of clustering effects. Identification of moderating factors, such as mental health symptoms, suicide behaviours, stigma and gender-role conflict, will be conducted by introducing three-way interaction terms of time × condition × moderator, also using MMRM. Analysis of binary outcomes will be undertaken using binary mixed models, analogous to linear MMRM.

Qualitative analysis of the semi-structured interviews will be conducted using Framework Analysis. Framework Analysis was designed for addressing social policy research questions [36] and has been used frequently in health research [37]. It follows a systematic process of inductive coding, generating a table of findings across participants that is conducive to interpretation and input from multiple researchers.

## Discussion

The need for effective and tailored interventions for personal and emotional problems in males is high, particularly given the rates of suicide and mental health difficulties observed in this population [1, 2]. The current project represents an opportunity to evaluate a program specifically designed for males, which primarily aims to increase help-seeking intentions for personal and emotional problems. The targeting of help-seeking intentions, and help-seeking attitudes and behaviours as secondary outcomes, within this program is important given the low rates of help-seeking evident in this population for mental health problems and suicide [5–8].

The intervention tested in this trial is also novel in its approach to targeting male gender-specific attitudes and obstacles that drive poor help-seeking intentions, attitudes and behaviours in this population. If found to be effective, it could provide a key solution to promoting help-seeking in young males, which is the cornerstone to preventing and reducing mental health problems, disengagement and suicide risk. Mental health and suicide prevention systems are lacking in Australian schools and the program tested in this trial has the potential to significantly impact the help-seeking intentions, attitudes and behaviours of young Australian men and stimulate more high quality research in this critical area.

Results of the study will be disseminated in peer-reviewed articles, conference presentations and in policy/practice forums relevant to schools, with a summary of findings posted on the website of the Centre for Mental Health Research for the information of participating schools, students and other stakeholders.

### Trial status

Participants are currently being recruited to the trial.

## Abbreviations

ACT: Australian Capital Territory
AHSQ: Actual Help-Seeking Questionnaire
ATSPPH-SF: Attitudes Toward Seeking Psychological Professional Help: Shortened Form
DQ5: Distress Questionnaire Scale – 5
GHSQ: General Help-Seeking Questionnaire
GRCS-A: Gender Role Conflict Scale - Adolescent Version
MHFA: Mental Health First Aid
MMRM: Mixed-model repeated measures
SSOSH: Self-Stigma of Seeking Help Scale
YRBS: Youth Risk Behaviour Survey
